### 2.5. Assessments

#### 2.5.1. Physical Activity Levels

Objective data of physical activity, including sedentary behavior (SB), light physical activity (LPA), moderate physical activity (MPA), vigorous physical activity (VPA), moderate-to-vigorous physical activity (MVPA), and total physical activity (TPA), are collected using accelerometers (GT3X, ActiGraph, Pensacola, FL). ActiGraph's GT3X accelerometers have been widely used in previous studies with preschoolers [27], children [28], and adolescents [29]. Except during water-based activities or while sleeping, the device is always worn on an adjustable belt positioned above the right hip.

During the first assessment wave, each accelerometer is set to collect physical activity data in counts units for each 1 sec epoch [30]. Cut-points for SB (<100 counts/min, cpm), MPA (≥1680 cpm), and VPA (≥3368 cpm) are consistent with previous related studies [31–33]. Floating Window algorithms will be used to define non-wear-time periods [34]. Each participant is instructed to wear the device for 7 consecutive days (including 5 weekdays and 2 weekend days). Participants with fewer than 3 days (2 weekdays and 1 weekend day) of valid accelerometer data (≥8 h per day) will be asked to redo the data collection wave.

To improve data correctness and completeness, research staff members will check the accelerometers worn by children every weekday morning in the kindergartens during the first assessment wave to ensure that they are functioning appropriately. Research staff members will also contact participant's parent or legal guardians every night using WeChat on cell phone during the 7-day monitoring period to ensure compliance and solve technical issues. Some teachers in primary and middle schools will be invited to join in the research group in order to help with checking the accelerometers during the following 5 assessment waves. This is because compliance monitoring may be difficult for research staff members due to the fact that the participants may be in many different schools.

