## 2. Methods

### 2.1. Research Design

The PACD study uses a long-term, longitudinal, cohort design. In the present study, 500 preschool children (3.5 to 5.5 years old) are taking part in 6 triennial assessment waves across 15 years.

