### 2.4. Procedures

Each group of participants is on their own assessment schedule that is dependent on the time of enrollment. In order to avoid data collection during the months when the participants may have unusual patterns of physical activity, such as summer and winter months, assessments take place during the spring (March through May) and fall (September through November). The anthropometric and physical fitness assessments are performed and managed during two different time periods. They are both performed and managed either at the kindergartens during the first assessment wave or at the Exercise and Fitness Sciences Center in Shanghai University of Sport during the following 5 assessment waves.

Following the obtainment of consent, point data collection is conducted within two weeks at each assessment. Participants perform anthropometric and physical fitness assessments, evaluation of cognitive development, blood sampling, and retrospective questionnaires and receive the objective devices (accelerometers) with instructions. With the assistance of research staff members, participants and parent/legal guardians complete the questionnaires. Then participants wear the accelerometers for 7 consecutive days (including 5 weekdays and 2 weekend days) in order to monitor their physical activity behavior [26]. Participants are instructed to continue with their normal daily routines during the sessions.

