### 2.6. Statistical Analyses

All of the collected data are typed into EpiData 3.1 software (EpiData Association, Odense, Denmark), double-checked by two research staff members, and exported to SPSS version 22.0 (IBM Corporation, USA) for further analyses. Descriptive statistics are used to present baseline data and the following assessment waves as mean ± SD and median (interquartile ratio, IQR) for normally distributed and nonnormally distributed data, respectively. Prior to analyses, the log and square root methods are used for nonnormally distributed data. Linear regression models are performed to examine the relation of physical activity and cognitive development over time in more detail, with LPA, MPA, VPA, MVPA, and TPA assessed by ActiGraph's GT3X accelerometers as the independent variables, Verbal IQ, Performance IQ, and Full Scale IQ as dependent variables, and data collected by retrospective questionnaires and anthropometric and physical fitness assessments as covariates or moderators [47]. Exploratory analyses are also performed in order to examine whether plasma IGF-1 and BDNF concentrations serve as the mediators for the potential positive effects of physical activity on cognitive development [48].

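### Accepting 3 to 7 valid accelerometer days, with no allowance for day-to-day error in the regression, is expected to attenuate single-exposure activity slopes, and could do so unevenly across waves

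*Protocol article*

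**What the plan says.** Section 2.4 has participants "wear the accelerometers for 7 consecutive days (including 5 weekdays and 2 weekend days", and section 2.5.1 repeats this target. Section 2.5.1 then sets the minimum: "Participants with fewer than 3 days (2 weekdays and 1 weekend day) of valid accelerometer data", where a valid day has "≥8 h per day) will be asked to redo the data collection wave". No exclusion is stated for a child who does not repeat.

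Section 2.6 states that "Linear regression models are performed to examine the relation of physical activity and cognitive development over time in more detail". The regressors are five activity variables from the accelerometer, and the outcomes are the three IQ scores. It does not say how valid days are combined into one value per child, and it mentions no weighting by number of days and no correction for measurement error.

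Two other places bear on the point. The Introduction asks whether the association is confined to certain ages, present throughout early life, or changing over time. Section 2.5.1 describes staff checking devices each weekday morning at the first wave. For the later waves it plans to rely on invited school teachers, because monitoring may be harder once children are spread over many schools.

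**The concern.** An average over a few days measures habitual activity with random error, because a child's activity varies from day to day. When one such variable is a regressor, classical error pulls its slope toward zero, and the pull is stronger with fewer days. The acceptance rule in section 2.5.1 and the model in section 2.6 are both written choices, so the point concerns how they work together.

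Two things are at stake. The activity slope is the study's main result, and readers will take it as the effect of habitual activity. The study also means to compare that slope across six waves. If the number of valid days changes with age, the attenuation changes too, and part of any apparent age trend would come from measurement.

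**Working it through.** The article gives no reliability, power or sample-size figure, so there is nothing to reproduce. The steps below start from the acceptance rule.

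**Inputs from the article.** Target 5 weekdays + 2 weekend days; minimum 2 weekdays + 1 weekend day (sections 2.4 and 2.5.1); linear regression on the accelerometer variables (section 2.6). The bracketed minimum is read as binding.

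**Assumptions, not in the article.** Single-day ICC of 0.3, 0.5 or 0.7; errors independent between days and of true activity; one activity variable in the model; where a mix is needed, children spread evenly over 3 to 7 valid days. The pilot (section 3) reports valid data for 86.1% of children but not how many days they had.

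**Step 1: what the rule allows.** Weekdays 2 to 5 and weekend days 1 or 2 give eight patterns, with these weekend shares: 2+1, 33.3%; 2+2, 50.0%; 3+1, 25.0%; 3+2, 40.0%; 4+1, 20.0%; 4+2, 33.3%; 5+1, 16.7%; 5+2, 28.6%. Valid days run from 3 to 7.

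**Step 2: attenuation at k days.** By Spearman-Brown, the reliability of a k-day mean is k × ICC / (1 + (k − 1) × ICC). This is also the slope's attenuation factor. For example, at ICC 0.3 and k = 3: 0.9/1.6 = 0.56.

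| ICC | 3 days | 7 days |
|---|---|---|
| 0.3 | 0.56 | 0.75 |
| 0.5 | 0.75 | 0.875 |
| 0.7 | 0.875 | 0.94 |

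**Step 3: an even spread over 3 to 7 days.** The mean of 1/k is (1/3 + 1/4 + 1/5 + 1/6 + 1/7)/5 = 0.2186. The slope ratio is 1 / (1 + ((1 − ICC)/ICC) × 0.2186):
- ICC 0.3: 1/(1 + 2.333 × 0.2186) = 0.662, a loss of 33.8%.
- ICC 0.5: 1/(1 + 0.2186) = 0.821, a loss of 17.9%.
- ICC 0.7: 1/(1 + 0.4286 × 0.2186) = 0.914, a loss of 8.6%.

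**Step 4: how much is due to short records.** Subtract the loss that remains with a full week:
- ICC 0.3: 33.8 − 25.0 = 8.8 points.
- ICC 0.5: 17.9 − 12.5 = 5.4 points.
- ICC 0.7: 8.6 − 5.8 = 2.8 points.

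**Step 5: across waves.** Take the extreme in which every child has 7 days at one wave and 3 at a later one, with the true slope unchanged. The observed slopes have ratio (3-day factor)/(7-day factor):
- ICC 0.3: 0.5625/0.75 = 0.75, an apparent fall of 25%.
- ICC 0.5: 0.75/0.875 = 0.857, a fall of 14%.
- ICC 0.7: 0.875/0.942 = 0.929, a fall of 7%.

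These are bounds, not forecasts.

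**Step 6: weekday/weekend mix.** If days were pooled as a plain mean, a 2+2 child and a 5+1 child with the same habits would differ by 1/2 − 1/6 = one third of the weekend-weekday gap. A simulation of 400,000 children made the eight patterns equally likely and let the gap range from 0 to 1 between-child SD. The attenuation factor moved from 0.667 to 0.663 (ICC 0.3), from 0.825 to 0.817 (ICC 0.5) and from 0.916 to 0.908 (ICC 0.7). Mix alone therefore changed it by less than 0.01 when day patterns were random.

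**The case against.** The strongest reply is that the article states nothing false. Seven days is the wear target and three days is the point below which a repeat is requested, so the two do not contradict each other. Few cohort articles spell out a measurement-error correction, and an unseen analysis plan may contain one. The article also has real safeguards: daily device checks at wave 1, nightly contact with parents, and repeat collection. If most children reach 6 or 7 days, so that the mean of 1/k is for example 0.15, the factor is 1/(1 + 2.333 × 0.15) = 0.74 at ICC 0.3 and 1/1.15 = 0.87 at ICC 0.5, close to a full week. All of this stands. It limits the size of the effect but does not remove the attenuation that remains at seven days or the possible drift between waves.

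A reader might infer three stronger claims that the article does not support:

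- **That the 3-day minimum causes the whole 18% to 34% loss (ICC 0.5 to 0.3).** Step 4 shows that 12 to 25 points of it are there with perfect compliance.
- **That children are compared on different kinds of week.** This needs a plain-mean rule, which the article never states. Silence on day weighting is detail that an article may leave to the full plan.
- **That activity effects are always underestimated.** This holds for one exposure with classical error. Section 2.6 lists five overlapping activity variables. If several enter one model, or if missing days depend on family factors, the bias can go either way.

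**Conclusion.** The point holds in a limited form. With the stated acceptance rule and model, a single-exposure activity slope is expected to be attenuated to between 0.56 (all children at 3 days, ICC 0.3) and 0.94 (all at 7 days, ICC 0.7) of its true value. Most of that comes from day-to-day variation that even a full week leaves. Shorter records add about 5 to 9 percentage points at ICC 0.5 to 0.3, and about 3 at ICC 0.7, if children are spread evenly over 3 to 7 days.

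The stronger reason to act is the comparison across ages. Section 2.5.1 itself makes fewer valid days at later waves plausible, and an unchanged slope could then appear to weaken by up to 25%, 14% or 7% for ICC 0.3, 0.5 or 0.7. The ICC and the distribution of valid days are assumptions throughout. The study's own day-level data can replace both.

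**What to change.** In section 2.6, add that at each wave the within-child day-to-day variance of each activity variable will be estimated from the recorded valid days. Beside the planned slope, report one corrected by regression calibration, or from a latent-activity model with days as indicators. The error variance should match each child's valid weekdays and weekend days, not only the total number of days. Report the distribution of valid days at each wave, so that a change in slope can be read against a change in measurement.

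As a clarification, state how days are combined. If they are averaged, weight weekday and weekend means 5:2, so that every child's value refers to the same week. This does not remove the attenuation.

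No new data are needed, only analysis wording and some programming. The corrected slope has a wider interval, and the correction does not recover lost power. The 5:2 weighting adds a little noise. In units of single-day error variance, a 5+1 child goes from 1/6 = 0.167 to (25/49)/5 + (4/49)/1 = 0.184, and a 2+2 child from 1/4 = 0.25 to (25/49)/2 + (4/49)/2 = 0.296. This is why the calibration must use the error variance of the weighted mean.

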#### 2.5.2. Cognitive Development

Two trained research staff members will evaluate the cognitive development of the participants at the first assessment wave using a short form of the Chinese Wechsler Young Children Scale of Intelligence (C-WYCSI) [35, 36]. C-WYCSI was established for Chinese young children (4–6 years old) based on the Wechsler Primary and Preschool Scales of Intelligence (WPPSI) which had been confirmed as a reliable measure of cognitive development in preschool children [37]. The reliability of C-WYCSI as a measure for Chinese young children has also been confirmed [35, 38]. To reduce the stress for a lengthy assessment of the participants, a short form of C-WYCSI assessment, which provides Verbal IQ (including Information and Picture Vocabulary subsets), Performance IQ (including Picture Completion and Block Design subsets), and Full Scale IQ scores, is used during the first assessment wave. Raw scores are then converted to standard scores according to a nationally standardized norm of China [36]. The short form of C-WYCSI assessment lasts approximately 40 min for each participant.

During the following 5 assessment waves, the Chinese Wechsler Intelligence Scale for Children (C-WISC) [39] (6–16 years) and the Wechsler Adult Intelligence Scale-Revised by China (WAIS-RC) [40] (>16 years) or their revised versions (if any) will also be used.

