## Abstract

The aim of the study is to investigate the relationship between physical activity as assessed by accelerometers and cognitive development across the human age ranges (from children and adolescents to adults). Additionally, this study seeks to explore whether physical activity contributes to cognitive development via modification of plasma insulin-like growth factor 1 (IGF-1) and brain-derived neurotrophic factor (BDNF). In the study, 500 preschool children (3.5–5.5 years old) are taking part in 6 triennial assessment waves over the span of 15 years. At each wave, participant measures included (a) 7-day physical activity monitoring using ActiGraph's GT3X accelerometers, (b) the evaluation of cognitive development, (c) anthropometric and physical fitness assessments, (d) plasma IGF-1 and BDNF concentrations, and (e) retrospective questionnaires. Linear regression models are used to examine the effect of physical activity on cognitive development; plasma IGF-1 and BDNF concentrations are considered as mediators into data analyses. The results of the study may help to inform future health interventions that utilize physical activity as a means to improve cognitive development in children, adolescents, and adults. Additionally, the study may assist in determining whether the putative effects occur via modification of plasma IGF-1 or BDNF concentrations.

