### 2.3. Participants

The participants were 500 preschool boys (*n* = 250) and girls (*n* = 250) living in urban areas of Shanghai, China. Participants were made eligible for the study after screening done via a questionnaire and a health assessment. Children were recruited from 8–10 kindergartens, based on the following inclusion criteria: (1) child is in the 2nd grade in kindergarten; (2) both child and parent/legal guardian are able to speak Mandarin; (3) informed consent is signed by the parent/legal guardian of the child. Conversely, exclusion criteria for the participants include the following: (1) health issues that limit physical activity; (2) mental illness; and (3) participation in special education programs [12]. The inclusion and exclusion criteria were assessed by two trained research staff members and doctors from the kindergartens and Xinhua Hospital affiliated to Shanghai Jiao Tong University School of Medicine. The anticipated gender breakdown is expected to be 50% male and 50% female.

Children Physical Health Research Base (CPHRB) in kindergartens was constructed before the study. Participants were recruited through a parents' information evening in the targeted kindergartens. Rewards for participants will be printed reports of the results of Intelligence Quotient (IQ) scores, physical fitness, anthropometric assessments, and so forth. If parental or legal guardian consent is given at recruitment, blood sampling is done and the printed reports for the results of blood trace element contents are provided. After the first assessment wave, both the family members of the participants who complete the assessments and the kindergarten teachers are provided with free assessment services of physical fitness.

Tracking plans are made for maintaining contact between family members of participants and the researchers, thus maximizing retention of participants. This has to be done due to the long-term period for data collection [24]. The longitudinal tracking plan includes (1) obtaining home and cell phone numbers and e-mail addresses; (2) establishing WeChat group and QQ group which have all the parents or legal guardians of participants; (3) providing all the participants and their family members with free assessment service for physical fitness annually; and (4) awarding certificates for recognizing their contribution to the longitudinal research [25].

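### The stated cohort age range starts at 3.5 years, half a year below the 4–6 year range given for the only wave 1 cognitive test, and no eligibility rule closes the gap

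*Protocol article*

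**What the plan says.** Section 2.1 of the protocol article gives the cohort and its schedule: "500 preschool children (3.5 to 5.5 years old) are taking part in 6 triennial assessment waves across 15 years". The Abstract gives the same age range.

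Section 2.5.2 names one cognitive test for wave 1. The task it gives to staff reads: "evaluate the cognitive development of the participants at the first assessment wave using a short form of the Chinese Wechsler Young Children Scale of Intelligence". On the scale's age range it says: "C-WYCSI was established for Chinese young children (4–6 years old". On scoring it says: "Raw scores are then converted to standard scores according to a nationally standardized norm of China". It does not state the age span of that norm.

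The criterion in section 2.3 that comes closest to age is "child is in the 2nd grade in kindergarten". The other inclusion criteria concern language and consent, and the exclusion criteria concern health, mental illness and special education. None sets a minimum age.

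Section 2.6 takes "Verbal IQ, Performance IQ, and Full Scale IQ as dependent variables" in the linear regression models.

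**The concern.** The bottom half-year of the stated cohort range lies outside the range stated for the test. The article offers no other test, separate norm, exclusion or sensitivity analysis for children aged 3.5 to under 4.

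Conversion to a standard score by an age-based norm is meant to take age out of the result. If the norm begins at 4.0 years, that cannot work for a younger child. Either no conversion exists, or the raw score is set against older children and comes out too low for the child's age. The error would then depend on age and would fall on all three wave 1 outcomes. Section 2.3 also promises families printed reports of the IQ scores, so a score outside the norm would reach parents.

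**Working it through.** The article gives no sample size, power or alpha figure that bears on this point. The check compares the stated ranges and then asks how many children could be affected.

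**Inputs**
- Cohort age at wave 1: 3.5 to 5.5 years (Abstract, section 2.1).
- Planned cohort: 500 (section 2.1). Enrolled at the time of writing: 346 (section 3).
- Wave 1 test: 4–6 years. Later tests: C-WISC 6–16 years and WAIS-RC over 16 years (section 2.5.2).
- Interval between waves: 3 years (section 2.1).

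**Step 1: the gap at wave 1**
- Lower end: 4.0 − 3.5 = 0.5 years not covered.
- Upper end: 5.5 is below 6, so there is no gap.
- The uncovered band is 0.5 of a 2.0-year range.

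**Step 2: later waves**

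Expected age is the wave 1 age plus 3 years per wave:

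| Wave | Expected age (years) | Stated test range |
|---|---|---|
| 2 | 6.5–8.5 | 6–16 |
| 3 | 9.5–11.5 | 6–16 |
| 4 | 12.5–14.5 | 6–16 |
| 5 | 15.5–17.5 | 6–16, then over 16 |
| 6 | 18.5–20.5 | over 16 |

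All are covered, so the problem is confined to wave 1.

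**Step 3: how many children could be under 4**

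The article reports no age distribution, so each row below is an assumption.

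| Assumed ages over 3.5–5.5 | Formula | Share under 4 | Of 500 |
|---|---|---|---|
| Uniform | 0.5 / 2.0 | 25% | 125 |
| Triangular, peak 4.5 | 0.5² / (2.0 × 1.0) | 12.5% | about 63 |
| Normal, mean 4.5, truncated at ±2 SD | [Φ(−1) − Φ(−2)] / [Φ(2) − Φ(−2)] | 14.2% | about 71 |
| Normal, mean 4.5, truncated at ±3 SD | [Φ(−1.5) − Φ(−3)] / [Φ(3) − Φ(−3)] | 6.6% | about 33 |
| Low case, set by assumption | none | 5% | 25 |

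The illustrative range is 25 to 125 of 500.

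**Step 4: does anything else in the article settle it?**

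The pilot correlation in section 3 (r = 0.90, n = 31) compares the short with the full form of the same scale. It does not show that the norm reaches below 4 years.

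**The case against.** The strongest reply is that the article never gives the age span of the norm. The range of 4–6 may be a rounded label, with tables that begin below 4.0. In that case there is no scoring error and one sentence closes the point. This stands, and it is why the conclusion is conditional. It does not remove the conflict between the two stated ranges.

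A second reply is that recruitment from a single kindergarten grade makes a uniform spread over two years unlikely, and 3.5–5.5 may be an outer envelope. This also stands: 25% is the top of the illustrative range. Still, the sponsor states 3.5 as the lower bound, so some children under 4 are to be expected.

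Three stronger readings are tempting but not supported:
- **A definite loss of 6 to 12 IQ points.** A reader might get this by taking ability as proportional to age: 100 × 3.5/4.0 = 87.5 and 100 × 3.75/4.0 = 93.8. The article describes standard scores from a norm, and nothing in it supports a ratio calculation. The figures also cover only the younger half of the band; on the same assumption the whole band runs from 0 to 12.5 points.
- **A biased wave 1 slope of IQ on activity.** This needs activity to vary with age within the cohort, which the article does not say.
- **Artificial gains by wave 2.** This needs an outcome defined as change from wave 1. Section 2.6 describes regression over time and defines no such outcome.

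Adjustment for exact age is commonly left to a fuller document that is not shown. Its absence from section 2.6 is not part of this finding.

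**Conclusion.** The point holds as a conflict between figures that the article itself states. The cohort begins at 3.5 years, the only wave 1 cognitive test is given for 4–6 years, and eligibility sets no minimum age. Followed as written, the plan lets children outside the test's stated range contribute to the wave 1 dependent variables.

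The mismatch of ranges is certain. The score error is conditional: it arises only if the norm does not extend below 4.0 years. The number affected is unknown, illustratively 5% to 25% (25 to 125 of 500) depending on the assumed age distribution. The size of the score error, and the direction and size of any bias in the activity–IQ association, cannot be derived from the article.

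**What to change.** 1. Establish the lower age limit of the cited norm, state it in section 2.5.2, and reconcile it with the age range in the Abstract and section 2.1. If the norm reaches 3.5 years, say so; steps 2 and 3 are then not needed.
2. If it does not, require each child not yet tested to be within the norm's span on the day of wave 1 cognitive testing. A younger child can move to a later spring or fall session under section 2.4. With a limit of 4.0 years, the longest wait is 4.0 − 3.5 = 0.5 years. Move the child's whole wave 1 assessment, so that the two-week collection window in section 2.4 is kept. Fix the 2nd-grade criterion at enrolment, so that a deferred child who changes grade stays eligible.
3. Count the children already tested below the limit, including pilot children merged into wave 1. Leave their wave 1 IQ out of the main regression models, keep their activity and later-wave data, and report a sensitivity analysis that includes those scores.
4. Include exact age at test in the model.

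**Cost.** A short amendment, some rescheduling and the loss of some wave 1 IQ scores. If the uniform case applied to the 346 already enrolled and all had been tested, the loss would be about 0.25 × 346 ≈ 86 scores; at 5% it would be about 17. Checking the norm first avoids discarding valid data. Recruitment was still under way at the time of writing, so a testing-age rule can cover at least the remaining 500 − 346 = 154 children.
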